### **Compliance Criteria**

The review process for this protocol is aimed at assuring correct contouring of target and critical structures, as well as appropriate SBRT planning. These reviews should avoid violations and deviations for this protocol. Each treatment shall be judged according to the protocol guidelines, with variations and deviations defined below:

#### Total Treatment Duration

Per protocol: All treatment falls within 14 calendar days

Variation Acceptable: All treatments fall within 16 days

Deviation Unacceptable: All treatments that take 16 or more calendar days to complete

#### GTV Compliance

Per protocol: no edits required

Variation acceptable: Variations in GTV or CTV other than deviation unacceptable

Deviation unacceptable: Definite HCC not contoured within GTV

#### PTV Compliance

PTV contouring per protocol: PTV > 4 mm and < 20 mm

Variation acceptable: PTV 3-4 mm or 20-25 mm

Deviation unacceptable PTV < 3 mm or > 25 mm

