|                                                                      | 
tumor known as the internal target volume (ITV) (if any) are then contoured on the 4-dimensional CT or breath-hold CT images. The planning target volume (PTV) which encompasses the ITV with a 2-3mm margin, takes the set-up errors into account. Doses of SBRT range from 35Gy to 50Gy in 5 fractions over 5 to 14 days as specified by RTOG 1112 protocol, a phase 2 study investigating the use of sorafenib in combination with SBRT for inoperable HCC. The final dose is determined such that a maximum tumoricidal dose can be delivered to the tumors while the doses to the organs-at-risk are within the set tolerance limits. Pretreatment positional verification by a cone-beam CT scanner, on-board imaging and/or other imaging devices available in each treating institution is done every time before SBRT with necessary correction if the linear and rotational displacement is more than 2mm and 2 degrees respectively. In addition, interval treatment verification with on-board x-ray imaging and cone-beam CT scan during SBRT may be performed additionally for identification of intra-fractional tumor displacement.
 |
| Safety Assessments                                            | 
Safety assessments will include the incidence, nature, and severity of adverse events, changes in vital signs and laboratory abnormalities grade per National Cancer Institute Common Terminology Criteria for Adverse Events (NCI CTCAE), version 4.0.
                                                                                                                                                                                                                                                                                                                                                                                                                                                                                                                                                                                                                                                                                                                                                                                                                                                                                             |

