## **4. STUDY TREATMENT**

### **4.1 Stereotactic Body Radiation Therapy (SBRT)**

Radical radiotherapy will be delivered by SBRT which is described as follows:

SBRT will be delivered by either a 10MV linear accelerator (TrueBeam, Varian Medical System, Palo Alto, USA) in the treating institution within 2 weeks of baseline investigations. Four-dimensional (4D) CT scanning for tracking the respiratory phases and radiation therapy planning is done with Real-time Patient Management (RPM) system (Varian Medical Systems, USA) or ExacTrac Adaptive Gating systems (Brainlab, AG, Germany) for motion detection. The gross tumor volume (GTV) with the co-registration of MRI and PET-CT images, and the motion of the tumor known as the internal target volume (ITV) are then contoured on the 4D CT images. The planning target volume (PTV) which encompasses the ITV with a 2–3mm margin, takes the set-up errors into account. Doses of SBRT range from 35Gy to 50Gy in 5 fractions over 5 to 14 days as adapted and modified from RTOG 1112 protocol, a phase 2 study investigating the use of sorafenib in combination with SBRT for inoperable HCC. The final dose is determined such that a maximum tumoricidal dose can be delivered to the tumors while the doses to the organs-at-risk are within the set tolerance

limits. Pretreatment positional verification by a cone-beam CT scanner, on-board imaging or other imaging devices available in each treating institution is done every time before SBRT with necessary correction if the linear and rotational displacement is more than 2mm and 2 degrees respectively. In addition, interval treatment verification with on-board x-ray imaging during SBRT may be performed additionally for identification of intra-fractional tumor displacement.

The details of target volume nomenclature and delineation as well as the acceptance criteria of SBRT are outlined in APPENDIX 1.

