The PTV will provide a margin around each ITVs to compensate for set-up. PTV nomenclature should follow GTV/CTV/ITV nomenclature guidelines. For example, PTV\_P for the PTV around the ITV\_P and PTV\_P1 and PTV\_P2 for PTVs around CTV\_P1 and CTV\_P2. A minimum PTV margin of 2–3 mm around each ITV is required in all directions. PTVs should not be manually modified due to proximity of adjacent OARs. The final PTVs should have dose annotated once the plan is final. Examples are PTV\_P1\_50 and PTV\_P1\_35 for targets treated to 50Gy and 35Gy, respectively.

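### The 2–3 mm PTV margin prescribed in the protocol is graded a variation or an unacceptable deviation by Appendix 1's own PTV Compliance bands

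*Protocol*

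**What the plan says.** Three places give the margin.

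- Protocol Synopsis, Radiotherapy Planning: the PTV "encompasses the ITV with a 2-3mm margin, takes the set-up errors into account". The same entry allows targets to be "contoured on the 4-dimensional CT or breath-hold CT images", so breath-hold planning is permitted.
- Section 4.1: the PTV "encompasses the ITV with a 2–3mm margin, takes the set-up errors into account". This section describes 4D-CT planning only and refers to Appendix 1 for delineation details and acceptance criteria.
- Appendix 1 (I), Target Volume Delineation: "The PTV will provide a margin around each ITVs to compensate for set-up", followed by "A minimum PTV margin of 2–3 mm around each ITV is required in all directions".

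Appendix 1, PTV Compliance, then grades the plan in three steps:

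- The best grade is worded "PTV contouring per protocol: PTV > 4 mm and < 20 mm".
- One step down, the tolerated range is given as "Variation acceptable: PTV 3-4 mm or 20-25 mm".
- The worst grade covers everything outside those ranges and is worded "Deviation unacceptable PTV < 3 mm or > 25 mm".

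These bands name no reference volume. Two further statements in Appendix 1 (I) matter. The clinical target volume (CTV) is expected to equal the GTV in most cases. For breath-hold treatment the ITV equals the GTV with no expansion. The Compliance Criteria say that every treatment is to be judged against these grades.

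**The concern.** A planning instruction and the scale used to grade it should agree, at least where the plan does exactly what it was told to do. Here the prescribed range (2–3 mm) and the per-protocol band (more than 4 mm, less than 20 mm) do not overlap. If both refer to the ITV-to-PTV margin, which is how Appendix 1 (I) defines the PTV, a planner who follows Section 4.1 to the letter cannot be graded per protocol.

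The stakes are limited but real for treatment quality assurance. SBRT is the only study treatment. The planner cannot tell which margin to draw. Two people reviewing one plan can grade it differently, depending on the volume each measures from. Reported rates of protocol-compliant treatment would then depend on an unstated convention.

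**Working it through.** **Inputs.** The prescribed set-up margin m is 2 to 3 mm (Synopsis; Section 4.1; Appendix 1 (I)). PTV Compliance grades a distance t as follows: t < 3 or t > 25 mm is unacceptable; 3 ≤ t ≤ 4 or 20 ≤ t ≤ 25 mm is a variation; 4 < t < 20 mm is per protocol. CTV expansion is taken as 0 (Appendix 1 (I), the expected case). Motion expansion x, from GTV to ITV, is 0 for breath-hold (Appendix 1 (I)). For free breathing the protocol gives no value, so a range is shown as an assumption.

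**Reading 1: t measured from the ITV, so t = m.**

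- m = 2 mm: t = 2, unacceptable
- m = 2.5 mm: t = 2.5, unacceptable
- m = 3 mm: t = 3, variation

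No value in the prescribed range is per protocol.

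**Reading 2: t is the total expansion from the GTV in a given direction, so t = m + x.**

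| Motion x (mm) | m = 2 mm | m = 2.5 mm | m = 3 mm |
|---|---|---|---|
| 0 (breath-hold) | 2, unacceptable | 2.5, unacceptable | 3, variation |
| 0.5 | 2.5, unacceptable | 3, variation | 3.5, variation |
| 1 | 3, variation | 3.5, variation | 4, variation |
| 1.5 | 3.5, variation | 4, variation | 4.5, per protocol |
| 2 | 4, variation | 4.5, per protocol | 5, per protocol |
| 3 | 5, per protocol | 5.5, per protocol | 6, per protocol |
| 10 | 12, per protocol | 12.5, per protocol | 13, per protocol |

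Solving 4 < m + x < 20 for x gives the per-protocol range of motion:

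- m = 2: 2 < x < 18 mm
- m = 2.5: 1.5 < x < 17.5 mm
- m = 3: 1 < x < 17 mm

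Solving m + x < 3 gives the unacceptable range at the low end: x < 1 mm for m = 2, x < 0.5 mm for m = 2.5, and none for m = 3.

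With x = 0 the two readings coincide. A breath-hold plan at 2–3 mm is therefore never per protocol on either reading.

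**What the choice of margin does to the volume.** As an illustration only, assume a spherical target with no motion and compare a 5 mm margin, which is inside the per-protocol band, with a 2 mm margin.

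- 3 cm tumour: (15 + 5)³ / (15 + 2)³ = 8000 / 4913 = 1.63, a PTV about 63% larger.
- 6.5 cm tumour: (32.5 + 5)³ / (32.5 + 2)³ = 52,734 / 41,064 = 1.28, about 28% larger.

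**The case against.** The best defence is that PTV Compliance is meant as total expansion from the GTV. Bands that reach 20 and 25 mm are implausible for a set-up margin of 2–3 mm, and the PTV Dosimetry table that follows separates PTVs around GTVs from those around other volumes, so the ITV is not the only frame of reference in these criteria. On that reading, ordinary free-breathing plans pass, and Section 4.1, which describes only 4D-CT planning, is contradicted only where motion expansion is about 2 mm or less. How often that happens cannot be judged, because the protocol gives no motion values. This narrows the conflict but does not remove it: the text does not state that reading, and breath-hold plans fail under it as well.

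A second defence is that Appendix 1 (I) calls 2–3 mm a minimum, so a margin above 4 mm satisfies every rule in the appendix. That is true, but such a margin departs from the Synopsis and Section 4.1, which give 2–3 mm as the margin itself. A stated minimum that is itself graded unacceptable or a variation is also not coherent.

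A third is that nothing turns on the grade. The protocol's explicit consequences are attached elsewhere: exclusion when the mean liver dose limit cannot be met at 35 Gy, and withdrawal for an interruption of more than 14 days. This stands, and it is why the point is minor.

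**Conclusion.** The inconsistency is real and minor. Measured from the ITV, the whole prescribed range is graded down: 2 to just under 3 mm is unacceptable and 3 mm is a variation. Measured as total expansion from the GTV, the conflict is confined to breath-hold plans and to free-breathing targets with motion expansion of at most 2 mm (2 mm margin) or at most 1 mm (3 mm margin). The breath-hold result does not depend on which reading is chosen.

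The second reading assumes no CTV expansion and grading direction by direction; the protocol does not say whether each, the smallest or the largest expansion is graded. No endpoint, analysis set, sample size or error rate is affected, and the liver and organ dose limits apply whatever the margin.

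**What to change.** State in Appendix 1, PTV Compliance, which volume the distance is measured from and whether each direction must meet the band. Then take one of three routes.

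1. **ITV-to-PTV margin, 2–3 mm intended.** Make the per-protocol band start at the intended floor, with no break at 3–4 mm, and grade anything below the floor unacceptable. The current text points to 2 mm, but a minimum written as 2–3 mm leaves the floor open, so the radiation oncology team should confirm 2 or 3 mm. The same team should set the upper variation and unacceptable limits.
2. **ITV-to-PTV margin, more than 4 mm intended.** Change the Synopsis, Section 4.1 and Appendix 1 (I) to match.
3. **Total expansion from the GTV intended.** Say so, and give breath-hold and low-motion targets their own band starting at the confirmed set-up margin.

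A separate slip in the same Compliance Criteria can be corrected at the same time. Under Total Treatment Duration, a course lasting 16 days falls in both the acceptable-variation and the unacceptable grade; the unacceptable grade should begin after 16 calendar days.

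The cost is wording only. Endpoints, sample size and visits are unchanged.

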#### PTV Dosimetry

Target coverage for each PTV should be considered on its own. If there are multiple tumors, the primary (dominant) PTV should be labeled #1. The intent is for prescription dose to cover 95% of each PTV. If PTVs are not treated as per guidelines, this is a deviation unacceptable. The PTV should be treated to as high a dose as possible, respecting normal tissue constraints (as mentioned below), as a dose response has been observed. Modifying required PTVs due to close proximity of adjacent OARs is not permitted.

The following table describes variations and deviations in the prescription dose (dose covering 95% of the PTV). Treating “per protocol” should always be the planning intent.

| Dose to 95% PTV              | PTVs around GTVs *                                       | PTVs around non-GTV ITVs/CTVs *                         |
|-------------------------------------|-----------------------------------------------------------------|----------------------------------------------------------------|
| Per protocol                        | Prescription dose +/- 5%                                        | Prescription dose +/- 5%                                       |
| Variation acceptable                | 90-95% or 105-110% of prescription dose, and $\geq 35\text{Gy}$ | 85-95% or 105-115% of prescription dose and $\geq 35\text{Gy}$ |
| Deviation unacceptable              | $< 90\%$ or $> 110\%$ of prescription dose, or $< 32\text{Gy}$  | $< 85\%$ or $> 115\%$ of prescription dose, or $< 32\text{Gy}$ |
| Overall plan deviation unacceptable | $< 32\text{Gy}$                                                 |                                                                |

\*Note that lower doses than the dose-allocation schedule are acceptable if they are required due to adjacent GI luminal structures that may limit the deliverable dose.

Compliance for Critical Structures (organs at risk, OARs) If non-hepatic OARs limit the prescription dose, the highest dose (from the 4 prescription doses) should be used, while maintaining OAR dose constraints.

| Prescription dose | Liver (minus GTV) mean dose |                      |                        |
|--------------------------|------------------------------------|----------------------|------------------------|
|                          | Per protocol                       | Variation acceptable | Deviation unacceptable |
| 50Gy                     | $\leq 13\text{Gy}$                 | 13-13.2Gy            | $> 13.2\text{Gy}$      |
| 45Gy                     | $\leq 15\text{Gy}$                 | 15-15.2Gy            | $> 15.2\text{Gy}$      |
| 40Gy                     | $\leq 15\text{Gy}$                 | 15-15.2Gy            | $> 15.2\text{Gy}$      |
| 35Gy                     | $\leq 15.5\text{Gy}$               | 15.5-15.7Gy          | $> 15.7\text{Gy}$      |

| Non-liver OARs         | Per protocol | Variation acceptable   | Deviation unacceptable |
|-------------------------------|---------------------|-------------------------------|-------------------------------|
| Esophagus max (to 0.5cc)      | 43Gy                | $> 43$ but $\leq 45\text{Gy}$ | $> 45\text{Gy}$               |
| Stomach max (to 0.5cc)        | 43Gy                | $> 43$ but $\leq 45\text{Gy}$ | $> 45\text{Gy}$               |
| Duodenum max (to 0.5cc)       | 43Gy                | $> 43$ but $\leq 45\text{Gy}$ | $> 45\text{Gy}$               |
| Small bowel (to 0.5cc)        | 43Gy                | $> 43$ but $\leq 45\text{Gy}$ | $> 45\text{Gy}$               |
| Large bowel max (to 0.5cc)    | 48Gy                | $> 48$ but $\leq 50\text{Gy}$ | $> 50\text{Gy}$               |
| Spinal cord + 5mm max (0.5cc) | 25Gy                | $> 25$ but $\leq 28\text{Gy}$ | $> 28\text{Gy}$               |
| Kidneys: bilateral mean dose  | $\leq 10\text{Gy}$  | $> 10$ but $\leq 12\text{Gy}$ | $> 12\text{Gy}$               |

The following organ dose constraints are guidelines, not mandatory:

Liver minus all GTVs:  $> 700\text{cc}$  and  $V10\text{Gy} < 70\%$

Heart max (30cc):  $< 30\text{Gy}$

Great vessel max (0.5cc):  $< 60\text{Gy}$

Skin (external) max (0.5cc):  $< 32\text{Gy}$

Chest wall max (0.5cc):  $< 50\text{Gy}$

Gallbladder max (0.5cc):  $< 5\text{Gy}$

Common bile duct max (0.5cc):  $< 50\text{Gy}$  (even though the bile duct is not often well visualized, it is always within the portal region and may be within high dose volumes for central targets, so efforts to reduce hot spots in this region are warranted)

**APPENDIX 2. Scanning algorithm of magnetic resonance imaging (MRI) scan with gadoxetate disodium injection**

MRI scanning was conducted with a 3-Tesla MR scanner (Philips Achieva 3.0T TX, Philips Medical Systems, Best, The Netherlands) throughout the whole study as shown below. The same scanner is used for all scans for all patients recruited into this study. MRI scans were performed at baseline, then at every 3 months until liver transplantation was performed or progressive disease was observed, whichever came earlier. All HCC lesions were evaluated by two independent radiologists and any discrepancy in determining the nature of the lesions was solved by consensus.

(1) T2-weighted TSE single-shot in 5mm section thickness

(2) Breath-hold triggered T1-weighted in-phase and opposed sequences in 7mm section thickness

(3) T2-weighted SPAIR with TE 80 and 160 in 7mm section thickness

(4) Diffusion-weighted single-shot echo planar imaging with respiratory triggering

(5) Gadoxetate disodium (0.025mmol/kg body weight)-enhanced dynamic phases: unenhanced, late arterial-phase, portal-venous phase, and delayed phases with T1-weighted three-dimensional (3D) turbo-field-echo sequence (T1 high-resolution isotropic volume examination, THRIVE) with a 2-mm section thickness and a FOV of 32-38 cm.

1038

1039 **APPENDIX 3. Positron-emission tomography with integrated contrast-enhanced computed**  
1040 **tomography (PET-CT) with two radiotracers (C-acetate [ACC] and F-**  
1041 **fluorodeoxyglucose [FDG])**

1042 Dual Tracer PET-CT scan was performed at baseline, and then every 3 months after SBRT  
1043 until liver transplantation done or until progressive disease whichever came earlier. All scans  
1044 were performed using the same scanner and protocol (Discovery VCT, 64-MDCT; GE  
1045 Healthcare Bio-Sciences Corp., Piscataway, New Jersey, USA). All patients are required to fast  
1046 for  $\geq 6$  hours, and the blood glucose concentration is  $\leq 8$  mmol/L before radiopharmaceutical  
1047 injection. ACC (440–590 MBq; 8.0 MBq/kg of body weight) was then administered  
1048 intravenously, and limited upper abdomen coverage acquired at 1 minute followed by a whole  
1049 body imaging is performed at 11 minutes after injection. Data acquisition with an integrated in-  
1050 line PET-CT scanner (Discovery VCT, 64-multislice CT; GE Healthcare Bio-Sciences Corp, NJ)  
1051 begins with non-contrast whole-body CT for attenuation correction, followed by PET with a 2-  
1052 minute emission acquisition time and a 16.2-cm axial field of view per position. At 45 minutes  
1053 after ACC injection, 330-520 MBq (6.3 MBq/kg of body weight) FDG was injected and the  
1054 same image acquisition was obtained at 60 minutes after FDG administration. Enhanced (with  
1055 Omnipaque 300, 2ml/kg; GE Healthcare) CT scanning with an in-house 3-phase (early and late  
1056 arterial and porto-venous) contrast-enhanced protocol covering the whole abdomen was then  
1057 performed for additional diagnostic evaluation. All HCC lesions were evaluated by two  
1058 independent radiologists and any discrepancy in determining the nature of the lesions was  
1059 solved by consensus.

1060 **Determination of MTV and TLG/TLA**

1061 Firstly, spherical volume of interests (VOI) with a diameter of 3cm were positioned in the right  
1062 lobe of liver at least 3 cm away from the tumors (if present) or the mediastinal blood pool if the  
1063 VOI cannot be reliably placed in the liver without being interfered by the adjacent tumor lesions  
1064 to determine the background standardized uptake value (SUV) as reference. The mean SUV  
1065 and standard deviation (SD) of these VOIs based on FDG and ACC were calculated and  
1066 recorded as  $SUV_{ref}$  and  $SD_{ref}$  respectively. For those patients whose lesion was seen with only 1  
1067 type of radiotracer, the same ROI was applied at the same level on the axial images of the other  
1068 radiotracer, correcting for any misalignment or misregistration of present. Background threshold  
1069 method was used to determine the threshold for subsequent delineation of the MTV as follows:  
1070  $Threshold = SUV_{ref} + 2SD_{ref}$ . TLG with respect to FDG or TLA with respect to ACC of any  
1071 tumor lesions is the product of  $SUV_{mean}$  and MTV of that lesion with respect to each  
1072 radiotracer. Only lesions that could be delineated using the threshold were deemed reportable  
1073 and were further measured using automatic segmentation using a GE advantage workstation.  
1074  $SUV_{max}$ , MTV and TLG/TLA were then computed. Lesions with metabolic activities less than  
1075 these threshold will be considered as “non-reportable”, and therefore “normal”. All these  
1076 parameters will be recorded as zero.

1077

1078

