|                           | 
fluorodeoxyglucose (FDG) and 11C-acetate (ACC) was proven to be more sensitive and specific to FDG-alone PET-CT scan in HCC diagnosis and staging. On the other hand, magnetic resonance imaging (MRI) with gadoxetate disodium is more accurate and sensitive to gadolinium-enhanced MRI and contrast-enhanced CT scan in detecting HCC and differentiate it from other non-HCC causes.
 
Based on the above, we are carrying out a phase 2 single-arm study on using SBRT as a bridging therapy before liver transplantation for HCC patients within LT criteria, monitored by pretreatment and posttreatment dual-tracer PET-CT scan and MRI scan with gadoxetate disodium.
                                                                                                                                                                                                                                                                                                                                                                                                                                                                                                                                                         |
| Study Design       | 
This study is a prospective phase 2, single arm study assessing the efficacy and safety of SBRT as bridging therapy in patients with HCC before LT, monitored by regular pretreatment and posttreatment dual-tracer PET-CT scan.
 
Radical radiotherapy will be delivered by stereotactic body radiation therapy (SBRT) with 35 to 50Gy in 5 fractions over 5 to 14 days.
 
Patient is mandatory to have histologically or radiologically confirmed HCC.
 
The co-primary endpoints of this study will be progression-free survival, and objective response. Patients will undergo tumor assessment with dual-tracer PET-CT scan and MRI scan with gadoxetate disodium at baseline, and then at 3 months and 6 months after SBRT and continuous interval dual-phase contrast CT scans every 3 months after SBRT for treatment response evaluation and surveillance by mRECIST, RECIST 1.1 and irRECIST until LT is done or when progressive disease develops.
 
Safety assessments will include the incidence, nature, and severity of adverse events, changes in vital signs and laboratory abnormalities grade per National Cancer Institute Common Terminology Criteria for Adverse Events (NCI CTCAE), Version 4.0.
 |

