### **1.1.5 Rationale for conducting this study**

In view of the above with, we are proposing a phase 2, single-arm study on SBRT as a bridging therapy before LT for HCC patients. MRI with gadoxetate disodium and dual-tracer PET-CT scan will be used as HCC diagnosis as well as treatment response evaluation following SBRT until LT is done or when progressive disease is documented. By doing so, it is hoped that these two imaging modalities will help identify those who truly fulfilled LT criteria so that LT will only be performed to those who are accurately and reliably diagnosed with the most contemporary imaging techniques.

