## 474 6.5 Efficacy Assessments

475 Screening assessments must include magnetic resonance imaging (MRI) with gadoxetate  
476 disodium as well as dual-tracer PET-CT with contrast enhanced triphasic CT scan of the liver  
477 for tumor contouring and treatment planning for SBRT.

478 Follow-up imaging with MRI with gadoxetate disodium injection and dual-tracer PET-CT  
479 scan with contrast-enhanced triphasic CT scans every 3 months after SBRT will be arranged  
480 for treatment response evaluation by RECIST 1.1, mRECIST, and PERCIST  
481 (APPENDIX 4 and APPENDIX 5) and surveillance for recurrence/relapse.

482 At the investigator's discretion, scans should be repeated at any time if progressive disease is  
483 suspected.

484 Confirmation of progression guidelines are set for the following reasons:

- 485 • for patient management and treatment decisions
- 486 • when scans are evaluated by two independent radiologists.

Confirmed objective disease progression refers to either of the following scenarios: 1. clinical progression/deterioration followed by a radiologic verification scan (progressive disease [PD] by RECIST 1.1, mRECIST, and PERCIST); or 2. in the absence of significant clinical deterioration, radiologic PD by RECIST 1.1, mRECIST, and PERCIST followed by a second radiologic confirmation scan with PD assessed according to the specific confirmation of progression criteria listed below. The confirmatory scan should occur preferably at the next scheduled imaging visit and no earlier than 4 weeks following the date of the immediate prior assessment of PD.

Immediate prior radiologic progression would be considered confirmed if any the following criteria are met in the confirmatory scan:

- $\geq 20\%$  increase in the sum diameters of target lesions (TLs) compared with the nadir at 2 consecutive visits, with an absolute increase of at least 5 mm in sum of diameters compared to nadir,

- and/or significant progression (worsening) of non-target lesions (NTLs) and/or of pre-existing new lesions at the confirmatory scan time-point compared with the immediate prior time-point (Note: Pre-existing new lesions are evaluated as NTLs at the confirmatory scan time-point),

- and/or additional new unequivocal lesions at the confirmatory scan time-point.

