If progression is not confirmed, in the absence of significant clinical deterioration, then the patient should continue the study and on-treatment assessments until the next PD which will also require a follow-up confirmation scan. If the first PD is not confirmed by the immediate next scan, then the Investigator should not change the PD assessment of the first scan.

If a patient discontinues treatment (and/or receives a subsequent anticancer therapy) prior to radiologic progression, then the patient should still continue to be followed until confirmed objective disease progression.

Following confirmed progression, patients should continue to be followed up for survival every 2-3 months until death or until patient refusal.

Please refer to APPENDIX 4 and APPENDIX 5 for the definitions of objective response by RECIST 1.1, mRECIST, and PERCIST. The method of determination of metabolic tumor volume (MTV) and total lesion glycolysis (TLG) and total lesion activity (TLA) based on PET-CT scan with FDG and ACC respectively for subsequent exploratory statistical analyses were described in APPENDIX 5.

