## **8.1 Analysis Endpoints**

### **8.1.1 Efficacy Endpoint**

#### **Primary**

- Progression-free survival (PFS)
  - PFS is calculated from the start of SBRT to the date of radiologically confirmed progressive disease based on RECIST 1.1, mRECIST, and PERCIST, or death from any cause
- Best objective response as defined by RECIST 1.1, mRECIST, and PERCIST

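### The protocol contradicts itself on whether tumor imaging ends at first or at confirmed progression, and the PFS definition does not say which scan dates the event

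*Protocol*

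**What the plan says.** Four places end imaging at transplant or at progression, and none asks that the progression be confirmed:

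- Appendix 2 (MRI): "then at every 3 months until liver transplantation was performed or progressive disease was observed, whichever came earlier".
- Appendix 3 (dual-tracer PET-CT): "until liver transplantation done or until progressive disease whichever came earlier".
- Synopsis, Study Design: "until LT is done or when progressive disease develops".
- Section 1.1.5: "until LT is done or when progressive disease is documented".

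Section 6.5 works differently. It accepts clinical deterioration followed by one verification scan. Otherwise it asks for two scans: "in the absence of significant clinical deterioration, radiologic PD by RECIST 1.1, mRECIST, and PERCIST followed by a second radiologic confirmation scan". On timing it says: "The confirmatory scan should occur preferably at the next scheduled imaging visit and no earlier than 4 weeks" after the scan that first showed progression. If the second scan does not confirm, "then the patient should continue the study and on-treatment assessments until the next PD which will also require a follow-up confirmation scan". Patients who stop treatment or start another anticancer therapy before radiologic progression are to be followed until progression is confirmed.

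The endpoint in Section 8.1.1 refers to confirmation: "PFS is calculated from the start of SBRT to the date of radiologically confirmed progressive disease", or death from any cause. It does not say whether the first or the confirming scan gives that date.

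**The concern.** The scan that completes a PFS event under Section 6.5 is taken after the point at which the appendices, the synopsis and Section 1.1.5 say imaging has ended. Both rules cannot be followed for a patient whose progression is seen on a scheduled scan without clinical deterioration.

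This bears on data collection for a primary endpoint. A statistical analysis plan can choose a censoring rule or an event date, but it cannot recover a scan that was never taken. Transplant ends imaging as well. A patient transplanted between the first progression scan and the confirming scan would therefore have no second pre-transplant scan, even if Section 6.5 were followed exactly.

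**Working it through.** The protocol states no PFS figure to reproduce: no null value, target, progression rate or success threshold. Its sample size (60% against 85%, 28 patients) concerns objective response and does not enter this point. The check is therefore the logic of the passages, then a conditional illustration.

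**1. Scheduled progression without clinical deterioration**

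| Rule followed | How PFS treats the case | Effect on PFS |
|---|---|---|
| Section 6.5, second scan taken | Event dated at first scan | None |
| Section 6.5, second scan taken | Event dated at second scan | Later by the gap between scans |
| Early stop, no second scan | First progression counted | None |
| Early stop, no second scan | Confirmation required, otherwise censored | Overestimated |

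The text of Section 8.1.1 does not exclude any of the four rows.

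**2. Size of the dating effect.** The minimum gap in Section 6.5 is 4 weeks, or 28/30.4 = 0.9 month. The preferred gap is the next scheduled visit, at 3 months. Dating at the confirming scan therefore adds about 1 to 3 months to each event confirmed that way.

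**3. Illustration of the fourth row (all rates assumed).** Let P be the 12-month risk of first progression, let 5% die by 12 months, and let f be the fraction of progressions that are symptomatic and so confirmed by one verification scan. With constant hazards:

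- True 12-month PFS = 0.95 × (1 − P)
- Reported 12-month PFS = 0.95 × (1 − P)^f

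| P | True | f = 0.5 | f = 0 |
|---|---|---|---|
| 20% | 0.760 | 0.850 | 0.95 |
| 30% | 0.665 | 0.795 | 0.95 |
| 40% | 0.570 | 0.736 | 0.95 |

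These are upper-end figures. They assume that nobody obtains the scan Section 6.5 requires, and they treat unconfirmed patients as having no extra risk of death, although death is always a PFS event. With 28 patients, one misclassified patient is 1/28 = 3.6 percentage points of a crude proportion.

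**4. Transplant before confirmation (assumed).** With a constant transplant rate and median wait m months, the chance of transplant within a 3-month confirmation gap is 1 − 2^(−3/m). This gives 0.293, 0.159, 0.083 and 0.042 for m = 6, 12, 24 and 48. The synopsis gives 6 months to 4 years as a typical range of treatment duration, not as medians. Progression may also take a patient out of consideration for transplant. The high end is therefore probably too high.

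**The case against.** The best defence is that Section 6.5 is the governing efficacy section. It orders the second scan, lets scans be repeated whenever progression is suspected, sets a 3-monthly schedule with no stop at first progression, and follows patients to confirmed progression. Section 6 cites Appendices 2 and 3 for scanning technique, so their stopping phrase could be read as shorthand for progression as Section 6.5 defines it. Section 6.8.5 also ties the end of tumor assessments to confirmed progression. This defence disposes of the stronger inference that asymptomatic progression can never be confirmed. It does not remove the conflict, because the synopsis and Section 1.1.5 repeat the early stop and nothing says which text prevails.

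A second defence is that PFS may not need the second scan at all. Section 6.5 gives patient management and reading by two independent radiologists as the reasons for its confirmation rule, and does not mention PFS. Inclusion criterion 1 uses the phrase radiologically confirmed simply to mean shown on imaging. Section 6.5 also tells the investigator to leave the first progression reading unchanged if the next scan does not confirm it. On that reading the first scan is the event and the early stop does no harm. The reading is possible, but the endpoint definition does not establish it.

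Third, event dating and the handling of intervening therapy are often left to the analysis plan. That is fair, and their absence alone would be no finding. They matter here because the protocol makes confirmation part of the endpoint while elsewhere ending the imaging that supplies it.

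Fourth, a single scanner per modality is specified for the study, so different practice at different imaging sites is unlikely. That stands; the risk is inconsistent handling between patients or readers, not between sites.

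**Conclusion.** The contradiction is real and concerns whether data for a primary endpoint are collected. Its effect is conditional. PFS could be overestimated if the early-stop wording is followed, PFS requires the Section 6.5 confirmation, and unconfirmed progressions are censored. If confirming scans are taken and supply the date, PFS is lengthened by about 1 to 3 months per event so confirmed. If the first progression scan is the event, there is no bias.

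A reader might infer that the error always favours the treatment. The documents do not support that: no passage says unconfirmed progression is censored, symptomatic progression needs only one verification scan, and death counts in every case. The percentages above rest wholly on assumed rates; the size of any bias cannot be computed from the protocol. PFS carries no numerical hypothesis, so no formal pass or fail decision changes. What is at risk is the PFS estimate itself.

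**What to change.** 1. In the synopsis, Section 1.1.5 and Appendices 2 and 3, reconcile the stopping wording with Section 6.5, so that progression-related imaging ends at confirmed progression as defined there.
2. In Section 8.1.1, state that a confirmed progression is dated at the first scan that showed it.
3. In the same place, state that a first progression followed by transplant or new anticancer therapy before a confirming scan is an event at that first scan and is not censored. Death before confirmation is already an event under the existing definition.

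The same amendment should check the PERCIST rule in Appendix 5. It asks for most metabolic progressions to be confirmed within 1 month, while Section 6.5 sets a minimum of 4 weeks and prefers the next 3-monthly visit.

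The cost is a wording amendment, and PFS may look slightly shorter. No scan is added beyond the one Section 6.5 already requires.
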